### Outcomes

2.5

The primary outcome is time, in days, to ‘relapse’ following recovery. Recovery is defined as the absence of significant symptoms and presence of adequate social functioning; and relapse as the return of significant symptoms and deterioration of social functioning [7]. A summary of each participant's social circumstances, mental health, and type of response from health care providers for the two-year follow-up period is created primarily from their electronic medical records and research contacts. This summary is reviewed by a panel of trained raters, blind to treatment allocation, who use it to estimate the presence and date of any recovery or relapse using an established method [7]. Any information that might unblind the panel is redacted, and the panel's estimation of allocation is monitored.

For a description of secondary outcomes, measures, potential mediators, and family/carer measures see Table 1 below.

**Table 1 t0005:** Details of secondary outcomes, potential mediators, and family/carer measures.

	Outcome	Measure	Description of measure
Secondary outcomes	Recovery	Time in days to initial recovery, and the total number of days spent in recovery [7]	An expert panel estimate based on 24 monthly summaries of a person's social circumstances, mental health, and type of response from healthcare practitioners. See assessment method described for the primary outcome measure.
	Service-user defined recovery	Questionnaire on the Process of Recovery (QPR) [40]	A 15-item self-report measure developed to assess intrapersonal and interpersonal functioning, measured at 3, 6, 12, and 24 month time points (test-retest reliability *r* = 0.769 [40]).
	Health-related quality of life	EQ-5D-5L [25]	A self-report measure yielding a 5-digit number describing self-rated health state measured, during the first research interview, and at 3, 6, 12, and 24 months post initial crisis presentation **(**intraclass correlation coefficient = 0.75 [30]).
	Service use and societal costs	Client Service Receipt Inventory (CSRI) [8] Plus the number of and length in days of psychiatric admissions, and number of accepted referrals to crisis services in the 24 months after the initial crisis	A tool used to collect information on service utilisation, accommodation, income, and other costs measured at 3, 12, and 24 months post the initial crisis presentation.
	Service user satisfaction	Client Satisfaction Questionnaire (CSQ-8) [6]	A self-report measure of service user overall satisfaction with care measured at 3, 6, and 24 months post initial crisis presentation (alpha coefficient, 0.83 to 0.94 [2]).
Potential mediators	Social network quality and size	Social Provisions Scale (SPS) [15]	A 24-item self-report measure that examines the degree to which respondent’s social relationships provide the dimensions of social support using a model of social provisions [60] measured during the first research interview, and at 3, 6, 12, and 24 months post initial crisis presentation. Scores range between 24 and 96 with a higher score indicating a greater degree of perceived support indicative of higher quality social networks (alpha coefficient, 0.89 [12]).
		Lubben Social Network Scale (LSNS-6) [33]	A 6-item self-report scale that assesses the size, closeness, and frequency of contacts of a service user's social network (family and friends), providing a total score between 0 and 30 during the first research interview, and at 3, 6, 12, and 24 months post initial crisis presentation. (alpha coefficient, 0.78 [12]).
	Shared decision making	The Modified Dyadic OPTION scale [36]	Assesses the degree to which clinicians involve patients in shared decision making through observer rating of clinician behaviour, measured at 3, 6, and 24 months post initial crisis presentation (alpha coefficient 0.9 [41]).
Family/carer outcomes	Carer satisfaction	Client Satisfaction Questionnaire (CSQ-8) [6]	A self-report measure of carer overall satisfaction with care measured at 3, 6, and 24 months.
	Carer burden	The Burden Assessment Scale [49]	A 19-item self-report measure completed by the primary caregiver to assess perceived objective and subjective consequences of providing care to a service user, measured at 3, 6, and 24 months, (alpha coefficient, 0.92 [27]).
	Shared decision making	The Modified Dyadic OPTION scale [36]	Assesses the degree to which clinicians involve carers in shared decision making through observer rating of clinician behaviour, measured at 3, 6, and 24 months.

We also collect diagnoses and service use in the 6 months before the index crisis (from medical records), and baseline demographic information and the Brief Psychiatric Rating Scale (BPRS), which assesses symptoms of severe mental illness by interview and observation. Scores range from 18 to 126 [45] (intraclass correlation = 0.78, [5]). Intervention receipt is logged for each participant throughout trial participation.

#### Sample size

2.5.1

Thirty clusters, with 19 participants each, provide an initial sample size of 570 participants, with a projected 540 participants being observed during the follow-up period. Following Freedman's [19] formula, a total of 157 participants was calculated as being needed to relapse during the 24-month follow-up period to detect an HR = 0.589 or more, with 90% power using a log-rank test at the 5% significance level. Following a method by Rutterford, Copas, and Eldridge [51], this number was inflated by our design effect (design effect = 1 + (obs. Per team cluster - 1) ICC = 1 + 17 × 0.04 = 1.68; based on a typical intra-cluster correlation in cluster randomised trials of ICC = 0.04; [18] to calculate the total number of relapses needed to adjust for clustering. This gives a requirement of 264 relapses during the 24-month follow-up period. Assuming an average relapse rate of 49%, this requires an effective sample size of 264/0.49 = 538 participants.

#### Blinding

2.5.2

The senior statistician, trial Chief Investigator (CI), and those assessing the primary outcome measure will remain blind to cluster allocation throughout the trial. All trial statisticians are blind to allocation during the randomisation process and prior to the approval of the Statistical Analysis Plan (SAP). Researchers collecting outcome data from participants and working with clinical teams are not blind to cluster allocation.

### Statistical analysis

2.6

The primary outcome, time to relapse from recovery, will be analysed using Cox regression, where time to relapse will be the dependent variable, with fixed explanatory variables of trial arm, and stratification factor (catchment area of the mental health service), and cluster-level balancing variables of general practice list size, and Index of Multiple Deprivation. The model will also contain a random intercept that varies at the level of the catchment area to account for general practice cluster effects.

This modelling will supply an estimate of the hazard ratio of relapse comparing Open Dialogue with TAU and an associated 95% confidence interval. In the (unlikely) event that covariates are missing or that aspects of the Open Dialogue intervention (e.g. number of contacts between participants and teams) drive censoring times, we will employ multiple imputation for survival outcomes as described in White and Royston [61].

Continuous secondary outcomes measured at several time points will be analysed using linear mixed models. In these models the available post-allocation measures of the secondary outcome variables form the dependent variable, with trial arm, time, trial arm x time interactions terms, stratification, and balancing variables as explanatory variables. To account for the correlation between repeated measures taken on the same subject, subject-varying random effects will be included in the model. To account for remaining correlation between outcomes from patients from the same cluster, a further cluster-varying random intercept will be included in the model.

Distributional assumption will be checked and continuous outcomes arising from skewed distributions suitably transformed before analysis.

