### Objectives

2.1

Primary objective: To examine whether Open Dialogue is more effective than TAU at increasing time to relapse after recovery.

Secondary objectives: To examine whether Open Dialogue is more effective than TAU at:-Reducing time to initial recovery, increasing overall days spent in recovery, and increasing service-user defined recovery-Reducing service use and societal costs and improving health-related quality of life-Increasing service-users' satisfaction with care

We will examine whether social network quality, social network size or shared decision-making mediate the impact on the primary outcome. Additionally, we will examine the experience of carer burden, shared decision-making, and satisfaction with care for the family/carers of a subsample of trial participants offered Open Dialogue or TAU.

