#### Statistical methods to handle missing data

2.6.2

All formal statistical analyses will follow the intention-to-treat principle. Estimates derived by fitting linear mixed models are valid in the presence of missing outcome values provided the missing data generating mechanism is missing at random (MAR). This particular MAR assumption allows all variables included in the analysis model to drive missingness. Multiple imputation will be employed should covariates be missing, or aspects of the interventions drive absence of outcomes. Details of any additional analyses will be described in the SAP.

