## Discussion

6

This paper presents details of the trial design, intervention delivery, and research processes of the first large-scale multi-site cluster randomised controlled trial of Open Dialogue, a person-centred, social network model of crisis and continuing mental healthcare. In this trial, adults presenting in crisis to mental health services in six areas of England are offered either Open Dialogue, or treatment as usual, and their mental health and service use monitored over the subsequent two years.

The trial seeks to assess whether Open Dialogue is more effective in helping individuals with severe mental illness to reach a state of recovery which is robust against relapses than Treatment as Usual. The trial participants are identified on the basis of experiencing a mental health crisis and the need for specialist secondary mental health care, rather than a specific diagnosis. This is not typical of other Open Dialogue and related research (e.g. [1,22,[54], [55], [56]]), but increases the generalisability of the results and the potential that Open Dialogue could provide an alternative to the functional team based model of mental healthcare [17]. In order to achieve this, exclusion criteria are kept to an absolute minimum. The inclusion of measures of cost, and a health economic analysis, will mean the economic viability of Open Dialogue as an alternative to usual care may also be established.

Monitoring of the delivery of Open Dialogue is an important part of this trial's design. The teams were established and deliver care within existing NHS service structures. For this reason the teams vary somewhat in their structure and relationship to existing services and are governed by different Trusts with different local policies and procedures, and varying care pathways. Adaptations to the model have been needed and were set out in operational requirements of an Open Dialogue Service within the NHS, and in particular to ensure that the intervention would be appropriate for those with depression, anxiety, eating disorders and personality disorders, as well as for those with psychotic disorders where much of the early work on Open Dialogue took place [48,56]. Maintaining a high-quality Open Dialogue service in this context can be challenging, particularly where structural changes impact on, for example, the re-organization of in-patient services and the development of a single points of entry for crisis referrals.

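### The primary Cox hazard ratio counts time from recovery, which Open Dialogue is meant to change, so it is conditional on recovering and is not the intention-to-treat comparison the protocol claims.

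*Protocol article*

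**What the plan says.** The Objectives section (2.1) gives the primary aim: "To examine whether Open Dialogue is more effective than TAU at increasing time to relapse after recovery". The Outcomes section (2.5) defines the endpoint to match: "The primary outcome is time, in days, to ‘relapse’ following recovery", with "relapse as the return of significant symptoms and deterioration of social functioning". A blinded panel judges from the two-year record whether each participant recovered or relapsed at all, and when.

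The Statistical analysis section (2.6) fixes the model: "The primary outcome, time to relapse from recovery, will be analysed using Cox regression". Its covariates are trial arm, catchment area, practice list size and deprivation index, plus a random intercept. None is an individual prognostic factor.

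The Objectives also list, as secondary aims for Open Dialogue, "Reducing time to initial recovery, increasing overall days spent in recovery, and increasing service-user defined recovery". The Discussion describes the overall aim as helping people "to reach a state of recovery which is robust against relapses".

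Section 2.6.2, on missing data, says without exception: "All formal statistical analyses will follow the intention-to-treat principle".

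**The concern.** Intention-to-treat means comparing everyone recruited according to the arm of their cluster. An outcome that begins at recovery is defined only for those who recover. Recovery follows randomisation and is itself a treatment target, so the two groups of recoverers need not be alike at the crisis, even if the arms were.

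Suppose more severely ill people recover later or less often, and also relapse more readily. If Open Dialogue brings more of them to recovery, it adds high-risk people to its own relapse risk set, and the hazard ratio moves against it. If it leaves them unrecovered, the hazard ratio moves in its favour. Either shift can occur with no effect on relapse. A participant who never recovers, a poor outcome by any reading, adds nothing to the primary estimate.

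Follow-up ends 24 months after the crisis, so time at risk after recovery is 24 months minus time to recovery and also differs by arm if recovery does. This harms the Cox model only if recovery time predicts relapse given the covariates, so it works through the same severity link and is not a second defect.

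**Working it through.** **1. The passages side by side.**
- Clock origin: recovery (2.1, 2.5, 2.6).
- Recovery follows randomisation: clusters are randomised before the crisis referral that forms baseline (4.2.1), and recovery is judged over the following two years (2.5).
- Recovery may not occur: the panel rates whether any recovery is present (2.5).
- Recovery is a treatment target: "Reducing time to initial recovery, increasing overall days spent in recovery" (2.1).
- Planned imputation (2.6, 2.6.2) covers missing covariates, and censoring or absent outcomes driven by the intervention. It does not cover a time to relapse that is undefined because recovery never came.

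The primary comparison as written is therefore conditional on a post-randomisation event, and the unqualified sentence in 2.6.2 does not describe it.

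**2. The plan's own figures, to set a scale.** Inputs from Sample size (2.5.1): HR 0.589, 90% power, 5% level (two-sided reproduces the figure), 18 observed per cluster, ICC 0.04.
- Freedman events: (1.960 + 1.282)² × (1.589/0.411)² = 157.06; stated 157.
- Design effect: 1 + 17 × 0.04 = 1.68. Events: 157 × 1.68 = 263.8; stated 264.
- Participants: 264/0.49 = 538.8; stated 538.

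The arithmetic reproduces. With 264 events and 1:1 allocation, the standard error of the log hazard ratio is about √(4 × 1.68/264) = 0.16.

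**3. How far selection could move the hazard ratio.** The documents give no recovery proportion, no link between severity and relapse, and no effect on recovery. All of these are assumed here.

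Setting A: latent severity U ~ N(0,1). The recovery hazard is multiplied by exp(−aU), a = 0.5 to 1.5, with median recovery 8 months at U = 0. The relapse hazard is −ln(0.42)/24 per month multiplied by exp(bU), b = 0.5 to 1. The window is 24 months, 74–85% of TAU recover, and there is no true effect on relapse.

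| Effect of Open Dialogue on recovery | HR among recoverers |
|---|---|
| None | about 1.00 |
| Recovery hazard 1.5 to 2 fold | about 1.04 to 1.14 (lowest values near 1.03) |
| Recovery moderately slowed | about 0.93 to 0.97 |

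A rerun for this note agreed. With the recovery hazard cut to two thirds it gave 0.92 to 0.97, and with it halved 0.87 to 0.95.

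Setting B fixes the proportions recovering instead, with severity again lowering recovery and raising relapse, and no effect on relapse:

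| TAU v Open Dialogue recovering | HR among recoverers |
|---|---|
| 70% v 70% | about 1.00 |
| 70% v 80% | 1.04 to 1.07 |
| 60% v 75% | 1.06 to 1.10 |
| 60% v 80% | 1.08 to 1.13 |

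With a true within-person HR of 0.589, Setting B gives 0.61 to 0.65 at 70% recovery in both arms and 0.65 to 0.75 at 60% v 80%. The gap between 0.589 and 0.61–0.65 arises even with equal recovery, from unmeasured severity. Only the further move goes with unequal recovery.

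**4. Against the standard error.** ln(1.04)/0.16 ≈ 0.2; ln(1.14)/0.16 ≈ 0.8; ln(0.93)/0.16 ≈ −0.5; ln(0.97)/0.16 ≈ −0.2.

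**The case against.** **Exclusion is not written.** No sentence says that non-recoverers leave the primary model. The sample size divides by 49% over all participants, as if all were at risk, and 4.3 leaves full analysis details to an SAP that is not shown. This stands, so exclusion is put here as the natural reading and not as a stated rule. It does not remove the point: the article itself fixes the outcome, the clock origin, the model and the intention-to-treat claim, and these do not fit together.

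**The estimand is declared.** The primary objective says openly that relapse is counted after recovery. True, and a conditional question is legitimate. What does not fit is calling its answer intention-to-treat.

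**Mitigation exists.** Time to initial recovery and total days in recovery are already secondary outcomes (Table 1). This stands and lowers the stakes. It helps interpretation without changing what the primary hazard ratio means.

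**The bias is modest and, if the trial's hypothesis on recovery is right, works against Open Dialogue.** That is fair for the simulated mechanism: at most about 0.8 standard errors. It rests on assumed inputs, and the sign reverses if Open Dialogue slows recovery.

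**A stronger reading.** A reader might infer that the primary result will be biased in a known direction, or that the trial is set to produce a false benefit. The document supports neither. It gives nothing from which direction or size could be found, and in the simulations a spurious benefit arises only when Open Dialogue slows recovery, contrary to its own objective.

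**Conclusion.** The point holds in this form: on its natural reading, the primary Cox hazard ratio is conditional on recovering, a post-randomisation event the intervention is meant to change, and the intention-to-treat statement in 2.6.2 does not describe it. That conclusion follows from the protocol's definitions and needs no simulation.

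The size of any bias is uncertain. With no true effect on relapse, the illustrations give hazard ratios of about 1.04 to 1.14 when recovery is 1.5 to 2 times faster under Open Dialogue, and about 0.93 to 0.97 when it is moderately slower, against a standard error near 0.16 on the log scale. These rest on an assumed severity that both delays recovery and raises relapse risk. Without that link, or with equal recovery in the arms, the shift disappears. The matter concerns what the headline result may be said to show; it does not establish that the result will be wrong.

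**What to change.** 1. In 2.6 and 2.6.2, state that the Cox hazard ratio from recovery is conditional on recovery and is not an intention-to-treat effect. Say how participants who never recover are handled.
2. Pre-specify beside it, as the comparison of all participants by randomised arm from the crisis date, total days in recovery over 24 months with non-recoverers scored 0. This is already a secondary outcome. Report the proportion recovering and time to recovery by arm with it, and interpret the relapse hazard ratio together with these.
3. Add a sensitivity Cox analysis adjusted for individual prognostic data from before the crisis: diagnoses and service use in the preceding 6 months, both taken from records. The BPRS is not a substitute, because it is taken at the first research interview, after the crisis and consent (4.2.1).

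Two tempting additions should be avoided. Days in recovery should not be a gate for claiming relapse prevention: it rises through faster recovery alone, and slower recovery could veto a real relapse effect. A multistate model may be reported for description, but its recovered-to-relapsed transition carries the same selection and should not be presented as removing it.

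The cost is wording plus two or three analyses on data already planned for collection, and a more qualified headline claim. It should be settled before the SAP is approved, while the statisticians are still blind to allocation (2.5.2).

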### Participant recruitment and retention

4.1

If a person presents to services and appears eligible, a local staff member asks if a researcher can make contact. Those who agree are contacted by a researcher with further information, and after time to consider (usually 48 h or as long as they need), they are asked for informed consent. If they lack capacity, consent via a personal (relative or friend) or nominated consultee (a local senior clinical professional consultee with no other involvement with the trial) may be sought [58], and reviewed at the point they regain capacity. Separate informed consent is sought from the family and carers of a purposive sub-sample of trial participants for questionnaires, and from all who attend a network meeting to audio-record that meeting.

Participants are also given a £15 shopping voucher for each interview and are reimbursed for any additional expenses (e.g. travel). For those participants who choose to withdraw from further participation, agreement is sought for access to their electronic medical records for the remainder of the study to allow for the primary clinical outcome to be collected.

Research staff are located within NHS sites, closely engage with clinical teams, and receive regular training, support, and supervision to effectively engage participants. Regular meetings with site-based Principal Investigators (PIs) and other senior clinical and management staff, and input from the Lived Experience Advisory Panel (LEAP) address any issues with participant recruitment and retention.

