#### Baseline and follow-up research interviews

4.2.1

The baseline timepoint is the date of the crisis referral. This referral takes place after cluster randomisation, but before a potential participant has been assessed as meeting eligibility criteria prior to consent. The first research interview is conducted as close as possible to the date of the crisis referral (baseline) after consent is provided. Research interviews either occur in person (i.e. at the research site or at participant's homes) or over the telephone (the primary method of data collection during the COVID-19 pandemic). Follow-up interviews are undertaken at 3, 6, 12, and 24 months from baseline (see Fig. 1).

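### Patients are recruited after cluster allocation by staff who are not blind, but the primary Cox model has no patient-level covariate although pre-crisis records are already extracted

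*Protocol article*

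**What the plan says.** **Order of events.** Section 2.3 allocates clusters of general practices to the arms. Section 4.2.1 takes the crisis referral as baseline and says of it: "This referral takes place after cluster randomisation". Eligibility assessment and consent come later still.

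**Who recruits.** Section 4.1: "If a person presents to services and appears eligible, a local staff member asks if a researcher can make contact". A researcher then gives information and seeks consent. Section 2.5.2: "Researchers collecting outcome data from participants and working with clinical teams are not blind to cluster allocation". Section 2.4 makes the care a patient receives depend on the cluster of their GP practice.

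**What the primary model contains.** Section 2.6 specifies a Cox model "with fixed explanatory variables of trial arm, and stratification factor (catchment area of the mental health service), and cluster-level balancing variables"; the balancing variables are practice list size and deprivation index. A random intercept is added for clustering. No characteristic of the individual patient enters. Patient-level confounders appear only in the mediation modelling of section 2.6.1.

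**What is collected.** Section 2.5: "We also collect diagnoses and service use in the 6 months before the index crisis (from medical records". Table 2 and section 4.2.2 show that these record data cover the crisis date and the preceding six months. They include diagnoses, drug and alcohol misuse, contacts and crisis referrals, and inpatient stays.

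**The concern.** Randomising clusters makes the clusters comparable in expectation. It does not make the recruited patients comparable if recruitment happens afterwards and those involved can know the arm. The restricted randomisation in section 2.3 balances two practice-level averages, which say nothing about which patients within a practice are approached or agree. The blinded outcome panel in section 2.5 protects against biased assessment of relapse, not against a different case mix in each arm.

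If recruits in one arm carried a heavier prior history, the stated model would attribute the resulting difference in relapse to Open Dialogue or to usual care. The pre-crisis record data are well suited to reducing this: they predate the care given for the index crisis, and they are plausible predictors of relapse. As the primary model is written, they are not used.

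**Working it through.** **1. The plan's own sample size, for scale.** Inputs from section 2.5.1: "to detect an HR = 0.589 or more", "with 90% power using a log-rank test at the 5% significance level", "a total of 157 participants was calculated as being needed to relapse during the 24-month follow-up period".

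- Freedman: (1.96 + 1.2816)² × ((1 + 0.589)/(1 − 0.589))² = 157.06 events (stated: 157).
- Design effect: 1 + 17 × 0.04 = 1.68, and 157 × 1.68 = 263.8 (stated: 264).
- 264/0.49 = 538.8 (stated: 538); 18 × 30 = 540 observed.

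These figures reproduce and are not in dispute. The calculation takes no credit for covariate adjustment.

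**2. How an imbalance reaches the hazard ratio.** Let a binary factor multiply the relapse hazard by g, with prevalence p₁ in Open Dialogue and p₀ in usual care, and let treatment have no effect. The initial hazard ratio in a model that omits the factor is about

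(1 + p₁(g − 1)) / (1 + p₀(g − 1)).

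The documents give neither g nor any prevalence, so both are assumptions.

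- g = 2, 40% v 50%: 1.40/1.50 = 0.933, a shift of about 7%.
- g = 2, 45% v 35%: 1.45/1.35 = 1.074, about 7% in the other direction.

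For the first case, the effective number of events is 264/1.68 = 157.1, so the standard error of the log hazard ratio is about 2/√157.1 = 0.160. The shift is ln(0.933)/0.160 = −0.43 standard errors, which raises the two-sided type I error from 5% to about 7.2%.

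**3. Simulation of the stated and the adjusted model.** The simulation used 2,000 runs per scenario and 320 independent patients (540/1.68 ≈ 321, to mimic the design effect). Relapse was 49% by 24 months, with one binary factor, recorded without error. Monte Carlo error on a 5% rate is about √(0.05 × 0.95/2000) = 0.5 points.

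True HR = 1, factor present in 40% of Open Dialogue and 50% of usual-care recruits:

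| Factor HR | HR, unadjusted | Type I error, unadjusted | HR, adjusted | Type I error, adjusted |
|---|---|---|---|---|
| 1.5 | 0.96 | 5.5% | 1.00 | 5.0% |
| 2 | 0.93 | 8.0% | 1.00 | 5.2% |
| 3 | 0.89 | 10.6% | 1.00 | 4.4% |

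True HR = 0.589, no imbalance (50% in both arms):

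| Factor HR | Power, unadjusted | Power, adjusted | Gain (points) |
|---|---|---|---|
| 1.5 | 89.6% | 89.8% | 0.2 |
| 2 | 88.4% | 90.7% | 2.3 |
| 3 | 85.7% | 91.3% | 5.6 |

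In a Cox model this gain arises because the conditional hazard ratio lies further from 1 (for a factor HR of 3, 0.588 adjusted against 0.616 unadjusted), not because the standard error falls. It is therefore a gain in power and should not be called precision.

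**The case against.** **The SAP may deal with it.** Section 2.6.2 leaves additional analyses to the SAP, and section 4.3 leaves it the full details. An adjusted supporting analysis may well be there, and its absence from the article is no fault. This stands for supporting analyses. It does not reopen the primary model, whose covariates section 2.6 lists; an adjusted sensitivity analysis would leave the headline estimate unchanged.

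**The stated model is coherent.** Adjusting for the stratification factor and the balancing variables matches the randomisation, and the trial was sized on a log-rank test. That is correct: the model is not erroneous. Adding patient covariates is an improvement, and it does change the target to a conditional hazard ratio.

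**Arm knowledge among local staff is not stated.** Section 2.5.2 says only that researchers are not blind. That the local staff member who makes the first approach knows the arm is inferred from care being tied to the cluster. The crisis referral itself can come by any permitted route and is not a choice made by trial staff.

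**Low enrolment does not show selection.** A reader might set the 65–75 crisis referrals a year in section 2.3 against 19 recruits per cluster. Section 2.2 implies about 14 to 25 open months per site, so 65 × 14/12 = 76 to 75 × 25/12 = 156 referrals per cluster, of whom 75–88% are not enrolled. The arithmetic is right, but the count precedes the exclusions in section 2.4 and includes people who decline. A large non-enrolled share is not a difference between arms, and the documents give no figure by arm.

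**Adjustment cannot cure recruitment bias.** It acts only on what is recorded. Unrecorded drivers, such as willingness to involve family, would remain. Nor are pre-crisis records the only individual data that allocation cannot affect: age and sex are equally safe. Nothing in the documents shows that these covariates would reduce variation between clusters. All of this stands.

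**Conclusion.** The point holds as a worthwhile, low-cost improvement to the primary analysis. Allocation precedes recruitment, the researchers are not blind, the primary model has no individual covariate, and suitable pre-crisis data are already collected.

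A reader might conclude that the trial is biased by recruitment, or that adjustment would put it right. The documents support neither. They contain no evidence of imbalance, and the sizes above rest on assumed inputs: a 10-point imbalance in one factor with a hazard ratio of 1.5 to 3, independent patients and perfect recording. Under those inputs a null hazard ratio moves to between 0.89 and 0.96 (0.93 for a factor that doubles the hazard), and type I error rises to about 5.5–10.6%. Adjusting for that factor brings it back to about 5%. The benefit without imbalance is about 0 to 6 points of power, negligible unless the covariates are strongly prognostic. The case rests mainly on protection against measured imbalance, with power a minor addition. It is confined to the primary model, as no check was made for the secondary mixed models.

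**What to change.** Before the SAP is signed off and before unblinding, name in the primary Cox model a short fixed set of individual covariates that predate the allocated care. Examples are diagnostic group, crisis referrals and inpatient stays in the six months before the crisis, substance misuse, age and sex. State how each is coded. Keep the model of section 2.6 as a sensitivity analysis, so that both hazard ratios are reported.

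Do not use the first-interview BPRS or EQ-5D for this purpose. The interview follows consent, and its scores may already reflect the allocated care.

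The interpretation should say that adjustment covers measured factors only. Reporting screening, consent and baseline characteristics by arm would let readers judge what remains.

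**Cost.** SAP wording. The record data are already extracted; age and sex are assumed to be part of the sociodemographic information in Table 2. The hazard ratio becomes conditional on the covariates, and a few missing values may need imputation, for which section 2.6 already provides. Section 2.5.2 keeps the trial statisticians blind until the SAP is approved, so the set can be chosen without knowledge of allocation.
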